### 2.4. Inclusion and Exclusion Criteria

Inclusion criteria include being pregnant with a gestational age ≤16, being over 18 years of age, understanding and speaking Spanish fluently, and giving consent to participate in the study. Additionally, participants must have access to the internet and a digital device (computer, tablet or smartphone). Those women who have a high-risk pregnancy or twins, are receiving pharmacological treatment for anxiety and/or depression or who do not give their consent will be excluded.

### 2.5. Adherence

Participants will be asked to participate in the activities proposed in each psychological content session and will be invited to put into practice what they learned during the week. To increase motivation and adherence, women will be able to contact the psychologist in charge of teaching the sessions if they have any questions or problems during the week.

### 2.6. Ethical Standards

This study is conducted according to the principles expressed in the Declaration of Helsinki, and has been approved by Comité Ético de Investigación de Galicia (CEIC) of Spain. All participants are guaranteed confidentiality of the information collected throughout the process. Participation will be completely voluntary and free, and no incentive (financial or otherwise) will be received for participation in the study.

### 2.7. Sample Size

Power calculations were conducted to determine the minimum sample size. As there was no research describing the efficacy of CBT delivered via videoconference in this population, power calculations were based on published RCTs of unguided CBT for antenatal depression [38]. To detect a between-group effect corresponding to Cohen’s d of 0.55, the minimum sample size for each group (α = 0.05, 80% power) was 53 participants. Therefore, we aimed to recruit a minimum sample of 140 participants to allow for expected attrition.

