### 2.2. Recruitment of Women

The midwives who collaborate in the research will invite pregnant women who attend obstetrics and gynecology consultations for pregnancy control and monitoring and who will give birth to their children in public hospitals in the Servizo Galego de Saúde (Spain) to participate in the study. Subsequently, the personnel in charge of the research will contact the women by telephone and again inform them verbally and in writing about the objective and methodology of the study. Once the consent form has been signed, the different questionnaires will be sent electronically. A questionnaire regarding sociodemographic variables (e.g., age, marital status, education level, employment status and personal monthly income), obstetric history and current pregnancy (e.g., number of previous pregnancies, planned pregnancy, complications) will be developed for this study.

After completion of the baseline questionnaire, participants will be randomly assigned to either the intervention or control group using block randomization, in a 2:1 ratio, using an online randomization program. Study personnel are unaware of which treatment group each participant will be assigned to at the time of the baseline assessment.

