### 2.8. Analysis Plan

The primary analysis will compare the mean scores of EDS-3A, STAI-E and GAD-7 between the two groups before and after the intervention and one month, 3 months and 6 months after the end of the intervention to evaluate the effectiveness of the protocol in preventing anxiety symptoms. Similar analyses will be performed for the secondary result on depressive symptomatology. For the GAD, the frequencies in the two groups will be compared at the same evaluation periods.

Regarding the effectiveness of treatment, descriptive statistics will be calculated for all questionnaires. Variance analyses for repeated measurements will be performed to compare the differences between each initial score obtained with the different administered questionnaires and the scores at T1 (end of treatment), T2 (after 1 month), T3 (after 3 months) and T4 (after 6 months) will be evaluated. Bonferroni post hoc comparisons will also be conducted. The number of evaluations compared will need to be taken into account to adjust the *p*-value in the Bonferroni test with the aim of minimizing type 1 errors. The treatment effect will be calculated using Cohen’s d for each of the follow-up times. The Reliable Change Index will be calculated for each time in order to determine any significant clinical changes occurring in each individual case post-treatment. To compare differences in GAD, the chi-square test and Fisher’s exact test will be used in the contrast of 2 × 2 tables. In addition, Cochran’s Q test will be used to determine the existence of differences across time points and McNemar’s test will be used to compare the differences in categorical variables between time points in a paired manner.

Data will be analyzed using the Statistical Package for Social Science (SPSS) for Windows version 23.0.

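### The 80% power in 2.7 belongs to one unadjusted between-group comparison; if the Bonferroni adjustment in 2.8 covers the group contrasts at each follow-up, their power is about 52–62%

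*Protocol article*

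**What the plan says.** Section 2.7 (Sample Size) sets the target: "To detect a between-group effect corresponding to Cohen’s d of 0.55", "the minimum sample size for each group (α = 0.05, 80% power) was 53 participants". The recruitment goal follows: "we aimed to recruit a minimum sample of 140 participants to allow for expected attrition". Multiplicity is not mentioned there, and neither are the scale, the visit or the test to which the 80% refers.

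Section 2.8 (Analysis Plan) describes a wider comparison. "The primary analysis will compare the mean scores of EDS-3A, STAI-E and GAD-7 between the two groups before and after the intervention", and again one, three and six months later. The model is a repeated-measures ANOVA: "Variance analyses for repeated measurements will be performed to compare the differences between each initial score" and the scores at T1 to T4. Bonferroni post hoc comparisons follow, with this instruction: "The number of evaluations compared will need to be taken into account to adjust the *p*-value in the Bonferroni test". No number of evaluations is given. The size of effect is reported visit by visit: "The treatment effect will be calculated using Cohen’s d for each of the follow-up times".

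Section 2.2 (Recruitment of Women) randomises "using block randomization, in a 2:1 ratio, using an online randomization program".

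**The concern.** The power statement and the analysis describe different tests. Section 2.7 is sized for one between-group difference judged at 0.05. Section 2.8 makes between-group means at several evaluations the primary comparison, reports an effect at each, and names Bonferroni as its only multiplicity adjustment. If a visit-level group contrast is judged after that adjustment, its threshold is stricter than the one used for sizing, and its power is below 80%.

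Interpretation is what is at stake. Someone who relies on the 80% could read a non-significant adjusted difference at a follow-up as fairly strong evidence against an effect of d = 0.55. With 53 per group and four evaluations, such an effect would be missed about 38.5% of the time (100 − 61.5), not 20%.

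**Working it through.** **Inputs.** From 2.7: d = 0.55, α = 0.05, power 80%, 53 per group (2 × 53 = 106 in total), 140 recruited. From 2.2: 2:1 allocation. From 2.8: follow-up evaluations T1, T2, T3 and T4, plus the initial one. Assumptions, because the article does not state them: two-sided testing, and a Bonferroni divisor k of 4 (the four follow-ups) or 5 (all five evaluations).

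**Formula.** For a two-sample t-test with n₁ and n₂ women, df = n₁ + n₂ − 2 and the noncentrality is δ = d × √(n₁n₂/(n₁ + n₂)). Power is the probability that a noncentral t with these parameters exceeds, in absolute value, the two-sided critical value at 0.05/k.

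**Step 1: reproduce the plan's figure.** With 53/53, δ = 0.55 × √(53 × 53/106) = 0.55 × √26.5 = 2.831 and df = 104. The critical value at 0.05 is 1.983, and power is 80.1%. The smallest n that reaches 80% is 53 per group by the t distribution (52 by the normal approximation). A one-sided test would need only 41 or 42. The stated 53 is therefore correct for one two-sided, equal-group, unadjusted comparison.

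**Step 2: apply the adjustment at 53/53.** For k = 4 the threshold is 0.05/4 = 0.0125, the critical value is 2.542 and power is 61.5%. For k = 5 the threshold is 0.05/5 = 0.01, the critical value is 2.624 and power is 58.3%.

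**Step 3: use the randomised ratio.** Splitting the same 106 completers 2:1 gives about 71 and 35. Then δ = 0.55 × √(71 × 35/106) = 0.55 × √23.44 = 2.663.

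| Women analysed | k = 1 (0.05) | k = 4 (0.0125) | k = 5 (0.01) |
|---|---|---|---|
| 53/53 | 80.1% | 61.5% | 58.3% |
| 71/35 (106 at 2:1) | 75.1% | 55.0% | 51.8% |
| 70/70 (140, no loss) | 89.8% | 76.4% | 73.9% |
| 93/47 (140 at 2:1, no loss) | 86.3% | 70.6% | 67.7% |

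Without adjustment, the 2:1 split of 106 lowers power by 80.1 − 75.1 = 5.0 points. At 53/53 the adjustment alone lowers it by 80.1 − 61.5 = 18.6 points (k = 4) or 80.1 − 58.3 = 21.8 points (k = 5). Even with all 140 women retained, the adjusted contrasts stay below 80%.

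**Step 4: sensitivity to what is not stated.** If all ten pairwise contrasts among five evaluations formed the family (k = 10, threshold 0.005), power at 53/53 would be 48.8%. In the other direction, adjusting for a baseline score correlated r with the outcome raises the effective effect to d/√(1 − r²). With r = 0.5 (assumed) that is 0.55/√0.75 = 0.635, and power at 53/53 is 76.5% (k = 4) or 73.9% (k = 5). With r = 0.6 it is 83.8% or 81.8%.

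**The case against.** The strongest objection is that 2.8 attaches Bonferroni to post hoc comparisons after the repeated-measures ANOVA. The sentence about the ANOVA sets the initial score against T1 to T4, so the post hoc tests can be read as contrasts between time points. With two groups, the group factor needs no post hoc test. On that reading the adjusted threshold never reaches the between-group difference for which 2.7 is sized. This objection stands as a real ambiguity, and it is why the result is conditional. It does not settle the matter. The same section makes between-group means at each evaluation the primary comparison and reports an effect size at each follow-up, so applying the adjustment to those contrasts is also a fair reading.

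Three further objections have weight.

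- **The divisor is not given.** The values 4 and 5 are assumptions, and the exact family may be left to a fuller document. Its absence is not the finding. The finding is that the stated 80% takes no account of an adjustment which the same article prescribes.
- **The ANOVA test is not said to be adjusted.** If the effect were constant at 0.55 over four follow-ups with between-visit correlation ρ (assumptions), the average of the four would have variance (1 + 3ρ)/4 relative to one visit. An unadjusted group test on that average at 53/53 would have power of about 94% at ρ = 0.5 and 89% at ρ = 0.7.
- **Precision and success rule.** Baseline adjustment could recover much or all of the loss, as Step 4 shows. A rule that counted success at any one of four adjusted visits would have power of about 83–89% for ρ between 0.7 and 0.5. The article claims no such gain in 2.7 and states no such rule.

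A reader might infer that power at every visit simply is 58–62%, or that the trial as a whole is underpowered. The documents support neither. The first treats an assumed divisor, equal groups and one reading of the post hoc step as fixed; the second overlooks the unadjusted ANOVA test.

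**Conclusion.** The point holds in conditional form. The arithmetic in 2.7 is correct, but its 80% describes one unadjusted two-sided comparison of two equal groups on one scale at one time point. If the between-group contrast at each follow-up is Bonferroni-adjusted for four or five evaluations, power for d = 0.55 is 61.5% or 58.3% with 53 per group, and 55.0% or 51.8% with the same 106 completers at 2:1. This assumes two-sided t-tests without baseline adjustment. It says nothing against the power of the repeated-measures ANOVA test. On either reading of the post hoc step, the article does not say which test has the 80%.

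**What to change.** In 2.7, make three changes:

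1. State that the 80% applies to a single unadjusted two-sided between-group comparison with 53 analysable women in each group.
2. Name the test and the time point that carry it.
3. If visit-level group contrasts fall under the Bonferroni adjustment in 2.8, give their power at the divisor used there and at the 2:1 allocation. For orientation, this is 55.0% for four evaluations or 51.8% for five, with 106 completers and no baseline adjustment. If the adjustment covers only contrasts between time points, say so; the lower figures then do not arise.

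This is a change of wording. No further recruitment is needed and the Bonferroni method can stay. The only cost is a less favourable stated power for the adjusted visit-level contrasts. Replacing Bonferroni with a fixed sequence of tests that starts at T1 would keep the full 0.05 for T1, but later visits could not be claimed if T1 failed. That is a design trade-off, and it is not needed to correct the statement.

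### The sample size is worked out for two equal groups of 53, but allocation is 2:1, so 140 recruits keep 80% power only up to about 14% attrition

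*Protocol article*

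**What the plan says.** Section 2.7 (Sample Size) sets the target effect: "To detect a between-group effect corresponding to Cohen’s d of 0.55". It then reports that "the minimum sample size for each group (α = 0.05, 80% power) was 53 participants", and concludes that "we aimed to recruit a minimum sample of 140 participants to allow for expected attrition". It gives no attrition rate, does not say whether the test is one- or two-sided, and does not mention unequal allocation.

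Section 2.2 (Recruitment of Women) says that women are "randomly assigned to either the intervention or control group using block randomization, in a 2:1 ratio". It does not say outright which arm is the larger; the word order points to intervention. Nothing elsewhere in the article adjusts the sample size for this ratio.

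**The concern.** A single minimum applied to both arms is an equal-allocation result. With 2:1 allocation the same total carries less information about a difference in means, and the two arms cannot both sit at the same minimum. Section 2.7 therefore justifies a design that section 2.2 does not run.

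At stake is whether the stated 80% power holds once the expected losses occur, and whether the section that justifies the trial's size describes the actual trial. No test or estimate becomes invalid because of this.

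**Working it through.** **Inputs.** From section 2.7: d = 0.55, alpha = 0.05, power 80%, 53 per group, 140 recruited. From section 2.2: ratio 2:1. Inferred: two-sided test, intervention the larger arm, attrition rate.

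**Method.** Two-sample t-test with noncentral t. The noncentrality is d × √(n₁n₂/(n₁+n₂)) on n₁+n₂−2 degrees of freedom.

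**1. Reproduce the plan's figure.** At 1:1 and two-sided 0.05, the required n is 52.9, so 53 per group, with power 80.1% (noncentrality 0.55 × √26.5 = 2.83). A one-sided test would need only 41 per group by the normal approximation, so the plan's figure is two-sided with equal groups.

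**2. Split 140 at 2:1.** 140 × 2/3 ≈ 93 and 140 × 1/3 ≈ 47. The smaller arm is 6 short of 53 at randomisation.

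**3. Requirement at 2:1.** The smaller arm needs 39.6, so 40, and the larger 80. The total is 120 and power is 80.4% (noncentrality 0.55 × √(80×40/120) = 2.84). The equal-group total is 2 × 53 = 106.

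**4. Attrition that 140 can absorb.** At 2:1: 1 − 120/140 = 14.3%. The allowance implied by the plan's own route is 1 − 106/140 = 24.3%.

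**5. Power for d = 0.55 with 140 recruits, by attrition** (equal loss in both arms, fractional group sizes kept):

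| Attrition | Completers at 2:1 | Power at 2:1 | Power at 1:1 |
|---|---|---|---|
| 0% | 93.3 + 46.7 | 86% | 90% |
| 10% | 84 + 42 | 82% | 86.5% |
| 15% | 79.3 + 39.7 | 80.1% | 84.5% |
| 20% | 74.7 + 37.3 | 77.6% | 82% |
| 24.3% | 70.7 + 35.3 | 75% | 80.1% |
| 30% | 65.3 + 32.7 | 72% | 77% |

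The threshold is about 14% with whole women (80 + 40) and about 15% with fractional sizes.

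**6. Detectable effect at the implied attrition.** With 71 and 35 completers, power for d = 0.55 is 75.1%, and 80% power is reached at d = 0.584.

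**7. Recruitment needed to keep 80% at 2:1.** 120/(1 − 0.243) ≈ 159 at the implied rate; 120/0.80 = 150 at an assumed 20%.

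**The case against.** The strongest reply is that a control arm below 53 is not in itself a loss of power. That is right. A reader might infer from 47 against 53 that the trial is underpowered from the outset, and the documents do not support that. The figure of 53 belongs to 1:1; at 2:1 the smaller arm needs 40, which 47 exceeds, and with no loss power is 86%.

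Second, the 24% is not the plan's figure. Section 2.7 says only "to allow for expected attrition". A reader might take 24% as the expected loss, but it is a back-calculation from 106 to 140. If the true expectation were 14% or less, 140 would suffice at 2:1. The section also calls 140 a minimum, so it is a floor. These points stand, which is why the result is given as a range. They do not remove the mismatch: the text derives 140 from the per-group figure of 53, and that derivation does not fit 2:1.

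Third, two inputs are inferred. Sidedness is settled by the reproduction of 53. Which arm is larger does not affect power, only whether the 47 are controls.

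Fourth, it might be said that adjusting for baseline would recover the loss without more women. The article does not support that as it stands. Restoring 80% at 71:35 requires 0.55/√(1−r²) ≥ 0.584, so r ≥ √(1 − (0.55/0.584)²) ≈ 0.34. The article gives no baseline–outcome correlation. Baseline is taken early in pregnancy and outcomes run to six months after the intervention, so such a value cannot be taken for granted at every time point.

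**Conclusion.** The inconsistency between sections 2.2 and 2.7 is real and the size basis is wrong as written. The plan's 53 per group is correct arithmetic for a 1:1 trial. For the 2:1 trial described, 80% power needs 120 completers (80 + 40), not 106, and 140 recruits support that only up to about 14% attrition. If attrition is the implied 24% (assumed, not stated), power is about 75%, some 5 points short, and the detectable effect moves from 0.55 to 0.58.

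The size is modest, and at low attrition there is no shortfall at all. The figures assume a two-sided t-test on one outcome, independent observations and equal loss in both arms. They are a like-for-like correction of the plan's own calculation. They are not an estimate of the trial's full power, since neither calculation allows for the three anxiety scales or for delivery in groups of 6–8.

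**What to change.** Rewrite section 2.7 for the ratio in section 2.2:

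- Replace 53 for each group with 80 + 40 completers (d = 0.55, two-sided alpha 0.05, 80% power), and name the larger arm.
- State the expected attrition rate and its basis.
- State the power that 140 recruits (about 93 and 47) give at that rate: for example 82% at 10%, about 78% at 20%, about 75% at 24%.
- Do not claim that baseline adjustment makes up the difference unless a correlation of about 0.34 or more is stated as an assumption.

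This costs only wording, provided the sponsor accepts the power shown. Keeping 80% at 2:1 with 24% attrition would instead mean about 159 recruits, 19 more than planned. If no one has yet been randomised, changing to 1:1 is the other route: 140 recruits then give 80% power at 24% attrition and the figure of 53 stands. It costs an amendment to section 2.2 and fewer women offered the intervention (70 rather than about 93, if intervention is the larger arm).

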### 2.8. Analysis Plan

The primary analysis will compare the mean scores of EDS-3A, STAI-E and GAD-7 between the two groups before and after the intervention and one month, 3 months and 6 months after the end of the intervention to evaluate the effectiveness of the protocol in preventing anxiety symptoms. Similar analyses will be performed for the secondary result on depressive symptomatology. For the GAD, the frequencies in the two groups will be compared at the same evaluation periods.

Regarding the effectiveness of treatment, descriptive statistics will be calculated for all questionnaires. Variance analyses for repeated measurements will be performed to compare the differences between each initial score obtained with the different administered questionnaires and the scores at T1 (end of treatment), T2 (after 1 month), T3 (after 3 months) and T4 (after 6 months) will be evaluated. Bonferroni post hoc comparisons will also be conducted. The number of evaluations compared will need to be taken into account to adjust the *p*-value in the Bonferroni test with the aim of minimizing type 1 errors. The treatment effect will be calculated using Cohen’s d for each of the follow-up times. The Reliable Change Index will be calculated for each time in order to determine any significant clinical changes occurring in each individual case post-treatment. To compare differences in GAD, the chi-square test and Fisher’s exact test will be used in the contrast of 2 × 2 tables. In addition, Cochran’s Q test will be used to determine the existence of differences across time points and McNemar’s test will be used to compare the differences in categorical variables between time points in a paired manner.

Data will be analyzed using the Statistical Package for Social Science (SPSS) for Windows version 23.0.

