## Abstract

**Background:** Anxiety is one of the most frequent disorders during the perinatal stage that is associated with adverse health effects in women and their babies. In spite of this, preventive interventions during this stage are scarce. A long-distance intervention carried out during pregnancy can be an effective and accessible resource to help improve women’s emotional state. The objective of this study is to present and assess the effectiveness of a telepsychology cognitive–behavioral preventive intervention during pregnancy to manage anxiety. **Methods:** A random clinical trial will be carried out among pregnant women in Spain. The psychological intervention will take place via videoconference in seven weekly sessions, lasting one hour each, with groups of 6–8 pregnant women. Study outcomes will be collected via online questionnaires at five points in time: pre-intervention (baseline: t0), post-intervention (baseline: t1), follow-up at 1 month (t2), follow-up at 3 months (t3) and follow-up at 6 months (t4). The control group will receive usual pregnancy care (attendance at pregnancy follow-up consultations and information and answers to frequently asked questions provided by the midwife). Our primary hypothesis is that the intervention will decrease the frequency of women who present anxious symptomatology during pregnancy. The second objective is to analyze the effectiveness of this intervention to prevent depressive symptomatology during pregnancy, as well as postpartum anxiety and depressive symptomatology. The primary outcome measure is the difference in the mean anxiety score between the intervention and control groups assessed by the Edinburgh Depression Scale-Anxiety Subscale (EDS-3A), the State–Trait Anxiety Inventory (STAI) and Generalized Anxiety Disorder Screener (GAD-7) at the end of the intervention and at 1, 3 and 6 months postpartum. Generalized anxiety disorder (GAD) will be evaluated with the SCID clinical interview at the same time points. The secondary outcome will be determined by using the EPDS at the same time points. **Conclusions:** The results will determine whether a cognitive behavioral therapy applied via videoconference is well accepted by pregnant women, and if it is effective in preventing anxiety and emotional symptoms during the perinatal stage. If this intervention is an effective and useful resource among pregnant women, it can be implemented as a tool in Spanish healthcare.

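### Repeated-measures ANOVA over five assessments reduces the effectiveness analysis to complete cases although the plan expects attrition; this wastes collected scores and may bias the arm comparison

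*Protocol article*

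**What the plan says.** Section 2.8 of the protocol article describes the questionnaire analysis in two steps. The aim comes first: "The primary analysis will compare the mean scores of EDS-3A, STAI-E and GAD-7 between the two groups before and after the intervention", and again at one, three and six months. The method follows: "Variance analyses for repeated measurements will be performed", setting each initial score against the scores at T1 to T4, with Bonferroni post hoc tests and Cohen's d at each follow-up. On software it says: "Data will be analyzed using the Statistical Package for Social Science (SPSS) for Windows version 23.0". The Abstract confirms five assessments, t0 to t4.

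Section 2.7 derives 53 women per group for d = 0.55, α = 0.05 and 80% power, and then says: "we aimed to recruit a minimum sample of 140 participants to allow for expected attrition". It gives no attrition rate and does not say whether attrition means loss by the last visit or any missed visit. Section 2.2 sets 2:1 allocation. The article names no mixed model, imputation or analysis set.

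**The concern.** Classical repeated-measures ANOVA needs a full row of scores. A woman who completes t1 to t3 but not t4 is removed from every visit, including those she attended. The primary objective (end of section 1) concerns anxiety during pregnancy, and t1 is the first assessment after the intervention. Under this method the t1 comparison is confined to women who also answered at t4, six months after the intervention by sections 2.1 and 2.3.1.

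Two things are at stake. The first is precision: scores that were collected go unused. This happens whatever the reason for the loss. The second is validity: the analysed women are selected by what they did after randomisation. If the reasons for leaving are related to anxiety and differ between arms, the completers are no longer a fair comparison. Different follow-up behaviour is plausible because contact differs. In the intervention arm, "women will be able to contact the psychologist in charge of teaching the sessions", and session 7 (section 3.2) includes the post-treatment evaluation and fixes the first follow-up date. Controls have appointments, midwife contact and prenatal classes (section 2.1), but the article describes no equivalent of these steps for them.

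**Working it through.** **1. The plan's own figure.** Normal approximation per group: n = 2(1.960 + 0.842)²/0.55² = 51.9, so 52. The exact two-sided t test gives 52.87, so 53, with power 80.1%. The stated 53 reproduces under 1:1 allocation.

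**2. Implied attrition.** 2 × 53 = 106, and 1 − 106/140 = 24.3%. This is derived, not stated.

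**3. Women with scores and women analysed, gradual loss.** Assume women leave for good at a constant rate, reaching 24.3% by t4. The rate per interval is 1 − (106/140)^(1/4) = 6.72%.

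| Visit | Women with a score | Used by the ANOVA |
|---|---|---|
| t1 | 130.6 | 106 |
| t2 | 121.8 | 106 |
| t3 | 113.6 | 106 |
| t4 | 106.0 | 106 |
| Sum | 472 | 424 |

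Discarded: 472 − 424 = 48 post-baseline scores, or 10.2%.

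**4. Power at t1 for d = 0.55, 2:1 allocation, two-sided 5%.** The noncentrality is 0.55 × √(n₁n₂/(n₁+n₂)), which under 2:1 is 0.55 × √(2N/9).
- N = 130.6: 0.55 × √29.0 = 2.96; t-test power 84%.
- N = 106: 0.55 × √23.6 = 2.67; t-test power 75%.

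The variance of the t1 difference scales as 1/N, so using all t1 scores lowers it by 1 − 106/130.6 = 19%. A simulated comparison with likelihood estimation (assumed visit correlations 0.40–0.66) gave standard deviations of 0.185 and 0.204: 1 − (0.185/0.204)² = 18%.

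**5. Skipped visits instead.** If each of the four follow-ups is missed independently with probability p (assumption), complete cases are 140(1 − p)⁴.

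| p | Women at any one visit | Power | Complete cases | Power |
|---|---|---|---|---|
| 5% | 133 | 84% | 114 | 78% |
| 10% | 126 | 82% | 92 | 69% |
| 15% | 119 | 80% | 73 | 59% |

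**6. Bias.** These are large-sample simulations; correlations and dropout mechanisms are assumed. Scores have unit SD, there is no true effect, and 24.3% are lost in each arm. Negative values favour the intervention.

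| Dropout mechanism | Completers' mean difference at t1 | Completers' change from baseline, t1 |
|---|---|---|
| Intervention arm only, log-odds 0.8 per SD of previous score | −0.14 | −0.01 |
| Same, log-odds 0.4 | −0.08 | −0.01 |
| Same mechanism in both arms, log-odds 0.8 | 0.00 | 0.00 |
| Intervention arm only, log-odds 0.8 per SD of change since baseline | −0.01 | −0.08 |

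The table uses correlations of 0.66 falling to 0.40; a constant 0.6 gives nearly the same values. In the last row the change contrast at t2 to t4 is −0.09 to −0.11. In a separate 600-trial simulation of the first mechanism, likelihood estimation on all scores was off by less than 0.01 SD at t1. With a true effect of −0.55 and one dropout mechanism in both arms, completers gave −0.54 to −0.56.

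**The case against.** **The article does not say listwise deletion.** It names no SPSS procedure, and a full protocol or analysis plan that is not shown could add imputation before the ANOVA. That is true, and silence on missing data is not the point. The point is the named method: followed as written, it needs complete rows, and the same article expects attrition.

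**Bias is not demonstrated.** A reader might infer that the main result will be biased. The documents do not support that. They say nothing on why women leave or whether this differs by arm. The quoted ANOVA sentence is about differences from the initial score, and that contrast is nearly unbiased when dropout follows the previous score. The 0.14 SD applies to the comparison of mean scores, which 2.8 gives as the primary comparison without itself limiting it to five-visit completers. The change contrast is not always protected (last row of the bias table), but that scenario is assumed too. The objection stands against any claim of certain bias.

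**24% is not the plan's rate.** Correct. It is inferred from 106 and 140. If the sponsor meant completers, the allowance already yields 106 of them. At 106 women, the gap between the planned 80% and 75% comes from applying a 1:1 calculation to 2:1 allocation, a separate matter. What deletion costs at t1 is the step from 84% to 75%. It shrinks at later visits and is nil at t4 under gradual loss.

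**Controls are not without contact.** A reader might think they only fill in questionnaires. Section 2.1 says otherwise, so the direction of any unequal loss is unknown.

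**Cochran's Q.** It also needs complete series, but its role is stated as "Q test will be used to determine the existence of differences across time points". The between-arm GAD comparison uses chi-square or Fisher tests visit by visit, so this concern does not reach it.

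**Conclusion.** The concern holds as a weakness of a stated method, and it should be fixed. It does not show that the trial's result will be wrong. Without imputation, repeated-measures ANOVA over t0–t4 turns the effectiveness analysis into a complete-case analysis in a trial that expects loss.

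Size, if the implied 24.3% is gradual loss by t4: about 131 women have t1 scores and 106 are analysed; about 10% of post-baseline scores go unused; power at t1 is about 75% rather than 84%. Intermittent gaps make it worse: at 10% missed per visit, 69% rather than 82%. The loss of data needs only that some women have partial series.

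Bias is conditional. It needs dropout that depends on anxiety and works differently in the two arms. In the assumed scenarios it reached about 0.14 SD for the mean score at t1, a quarter of the planning effect (0.14/0.55 = 0.25), and was near zero when dropout worked the same way in both arms.

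**What to change.** In section 2.8, replace the repeated-measures ANOVA with a linear mixed model for repeated measures (SPSS MIXED, REML) for each questionnaire score:
- Fixed terms: arm, visit, arm × visit and the t0 score. Within-woman covariance: unstructured, which also removes the sphericity assumption.
- Analysis set: all randomised women with at least one follow-up score, in their allocated arm. With t0 as a covariate, a woman with no follow-up score contributes nothing. If every randomised woman is to contribute, model t0 as an outcome instead.
- Estimates: the arm difference at each of t1 to t4, taken from this model.
- A sensitivity analysis under missing-not-at-random. Complete-case ANOVA may stay as a further sensitivity analysis.

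Cost: wording in 2.8 and slightly more modelling work. No new visits, data or software are needed. The mixed model relies on missing-at-random given the observed scores. That is an assumption too, though weaker than what the complete-case analysis needs, and it is why the sensitivity analysis belongs in the plan. The change should be made before the data are analysed.
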